### Sample size

The sample size was calculated based on results from previous literature regarding primary outcome (adherence to medication) in cardiological studies [22, 26]. Statistical power analysis using IBM SPSS Sample Power 3 (IBM Corp., Armonk, NY, USA) showed that a required sample size of 186 participants was needed to detect a statistically significant increase in adherence to prescribed BMT from 50 to 70% (power, 0.80; significance value, 0.05; two-sided). We plan to recruit 210 participants and expect a 10% drop-out.

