### Randomisation

Randomisation is performed by sequence generation using secure computer-generated random numbers. The allocating study nurses have no insight to block randomisation factors behind the sequence generation process. Patients who meet all study criteria and consent to participate are randomised to either the intervention group or the control group. No blinding will be applied in this study.

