### Data collection

#### Biomarkers

Biomarkers will be measured at study enrolment and at 1 year after revascularisation. Blood samples will be collected to assess HbA1c, triglyceride, high- and low-density cholesterol, and total cholesterol levels. An exhalation test for measuring carbon monoxide, the piCO™ Smokerlyzer® (Bedfont® Scientific Ltd., Kent, England), will be used to assess smoking status.

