### Statistical analysis

Descriptive statistics will be used to describe baseline demographic and clinical data. Continuous variables will be summarised as mean (SD) or median (interquartile range), and categorical variables will be summarised as number (percentage). Comparisons between the intervention group and the control group will be made using the t-test and ANOVA for repeated measures, or the Wilcoxon rank-signed test and Kruskall–Wallis test according to the underlying distribution for continuous data. The chi-square or Fischer’s exact test will be used for categorical data. Logistic regression analysis will be performed for binary outcomes to adjust for confounding factors. All analyses will be performed according to the intention-to-treat principle. IBM SPSS version 23 or later (IBM Corp., Armonk, NY, USA) will be used for statistical analyses. The CONSORT 2010 statement will be followed when reporting the results [46].

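### The paired Wilcoxon signed-rank test is named for comparing two independent randomised arms; the rank-sum test should replace it

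*Protocol article*

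**What the plan says.** The Statistical analysis section of the protocol article gives the purpose of the tests first: "Comparisons between the intervention group and the control group will be made using the t-test and ANOVA for repeated measures". It then gives the alternatives for data that do not suit those methods: "or the Wilcoxon rank-signed test and Kruskall–Wallis test according to the underlying distribution for continuous data". Categorical data are handled separately: "The chi-square or Fischer’s exact test will be used for categorical data", with logistic regression for adjusted analysis of binary outcomes. No rank-sum or Mann-Whitney test is named anywhere in the article.

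The design is parallel-group. Under Randomisation: "Patients who meet all study criteria and consent to participate are randomised to either the intervention group or the control group". No matching or crossover is described.

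Pairs do exist within patients. Under Biomarkers: "Biomarkers will be measured at study enrolment and at 1 year after revascularisation". The Clinical assessments section sets the same two times for blood pressure and body measures, and three times for the ankle brachial index (ABI): enrolment, 4–8 weeks and 1 year.

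**The concern.** The named test does not fit the stated task. A signed-rank test ranks the differences within pairs. A patient in the intervention arm has no partner in the control arm, so there are no pairs to difference.

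An analyst following the text must therefore guess. The wording could be a slip for the rank-sum test, or it could mean a test of change within each arm from enrolment to 1 year. These are different analyses, and the text does not say which is meant.

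The second reading matters in this design. The Recruitment section places baseline data collection before surgery and randomisation after it, and both arms are operated on. Outcomes that surgery itself should move, such as ABI, walking distance and quality of life, can change from baseline in both arms whether or not the follow-up programme works. A significant change within one arm says nothing about the programme.

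**Working it through.** 1. **The plan's own figure, to fix the scope.** Inputs from Sample size: "increase in adherence to prescribed BMT from 50 to 70% (power, 0.80; significance value, 0.05; two-sided"). Equal allocation is assumed, as the ratio is not stated. With pooled variance and no continuity correction, n per arm = [1.960 × √(2 × 0.6 × 0.4) + 0.842 × √(0.5 × 0.5 + 0.7 × 0.3)]² / 0.2² = (1.358 + 0.571)² / 0.04 ≈ 93, or 186 in total, with power 0.800. This agrees with "a required sample size of 186 participants was needed". It is a calculation for two proportions, so no choice of rank test changes it. A primary outcome analysed as that proportion goes to chi-square, Fisher or logistic methods, not to the rank tests.

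2. **Signed-rank test on unpaired arms.** The statistic uses d(i) = x(i) − y(π(i)), where π says which control patient is set against intervention patient i. It sums the ranks of |d(i)| over the positive differences. With no matching in the design, π is arbitrary, and the result changes with it. In one simulated skewed data set of 93 per arm (log-normal, one arm shifted by 0.3 on the log scale), 2000 random pairings of the same values gave:

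| Quantity | p-value |
|---|---|
| Signed-rank, lowest | 0.025 |
| Signed-rank, 2.5th percentile | 0.067 |
| Signed-rank, median | 0.221 |
| Signed-rank, 97.5th percentile | 0.454 |
| Signed-rank, highest | 0.585 |
| Mann-Whitney (needs no pairing) | 0.033 |

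These are illustrative data, not trial data.

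3. **Unequal arms.** The plan recruits 210 and expects 10% drop-out: 210 × 0.9 = 189. That is an odd number, so at exactly the expected loss the arms cannot be equal. The signed-rank test then cannot be computed without discarding someone.

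4. **Kruskal-Wallis with two arms.** Let N = n1 + n2, let R1 be the rank sum of arm 1, and let D = R1 − n1(N+1)/2. The mean ranks of the two arms depart from (N+1)/2 by D/n1 and −D/n2. So, without ties, H = 12/[N(N+1)] × D²(1/n1 + 1/n2) = 12D²/[n1 n2 (N+1)]. This is the square of the rank-sum Z, whose variance is n1 n2 (N+1)/12. The two tests therefore give the same two-sided asymptotic p-value when no continuity correction is used. Numerically, the largest difference was about 2e-12 over 500 simulated skewed data sets of 93 per arm, and about 1e-11 over 200 data sets with tied scores.

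5. **Repeated measurements.** Kruskal-Wallis treats all observations as independent. It suits one value per patient at one time. It takes no account of the three ABI values from the same patient, so it is not a rank counterpart of repeated-measures ANOVA.

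**The case against.** The strongest reply is that the plan already names a valid test. Kruskal-Wallis stands in the same phrase and, with two arms, does the work of the rank-sum test. This stands. A reader might infer that non-normal outcomes are left with no valid comparison between arms; the text does not support that.

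A second reply is that the wording is a slip. Kruskal and Fisher are both misspelt nearby, so test names are written loosely, and a test that cannot be run on unequal arms would be noticed. That is plausible, but the article cannot settle it. The statement is positive and wrong, so neither a separate analysis plan nor the condensed form of an article accounts for it.

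A third reply is that the sentence does not say its parametric and rank tests correspond in order, so Kruskal-Wallis may never have been meant to replace repeated-measures ANOVA. This also stands. The point on ABI is a caution about how the list may be read, not a second established error.

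A reader might go further and suppose that the investigators will test each arm separately and claim an effect when only one arm is significant. With no true difference between arms, exactly one arm would be significant with probability 2p(1−p), where p is the within-arm power: 50%, 32% and 18% at p = 0.5, 0.8 and 0.9. For a claim in favour of the programme alone, the chance is half of that: 25%, 16% and 9%. The arithmetic is right, but the article describes no such procedure and gives no within-arm power. Its sentence speaks of comparison between the groups. These figures are not a measure of this error.

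**Conclusion.** The error is real and narrow. A paired test is assigned to a comparison of independent arms, and as named it cannot validly make that comparison. It affects only the signed-rank test, and only continuous secondary outcomes that turn out non-normal; the article does not say which those will be. Kruskal-Wallis remains valid for two arms at a single time. The sample size of 186 is unaffected. So is the primary outcome, on the assumption that it is analysed as the proportion for which the trial was powered.

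No numerical bias can be attached to the wording, because the test cannot be run between arms in any one agreed way. The simulated range of p-values shows how much an arbitrary pairing could matter; it does not predict what this trial would report. This is a should-fix correction of secondary analyses.

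**What to change.** In the Statistical analysis section, replace the signed-rank test with *the Wilcoxon rank-sum (Mann-Whitney) test for comparisons between the two arms at 1 year*. Kruskal-Wallis may stay; with two arms it becomes redundant but does no harm. Removing it without naming the rank-sum test would take away the only valid between-arm rank test now listed.

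Add that *any signed-rank test of enrolment against 1 year within an arm is descriptive only and is not evidence of a programme effect*, because baseline precedes surgery and both arms have surgery. Make clear that Kruskal-Wallis is for a single time and is not the rank version of repeated-measures ANOVA. If non-normal ABI is to be analysed across its three times, name a method that allows for repeated measurements.

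The cost is a sentence or two, with no new data and no change to the sample size. The Trial status section reports that data collection is still under way, so the correction can be recorded before the analysis.

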### Study design and setting

The FASTIC study is a multicentre, randomised controlled clinical trial. Patients will be recruited from two sites; the Departments of Vascular Surgery at Södersjukhuset and at Karolinska University Hospital, both in Stockholm, Sweden. Patients with IC are referred to the vascular surgical outpatient clinics in one of these hospitals by a primary care physician.

The Stockholm County is a geographical area covering the City of Stockholm and surrounding area with approximately 2.3 million inhabitants. This region has two centres for vascular surgery, the Karolinska University Hospital and Södersjukhuset, both of which are located near the city centre. On average, 350 open surgical interventions and endovascular interventions for patients with IC are performed at these two centres every year according to the Swedish National Registry for Vascular Surgery (Swedvasc). No major vascular surgery is performed outside these centres and all patients in the Stockholm County with IC who may require arterial surgical intervention are referred to one of these centres. During the first visit at the vascular surgical outpatient clinic, diagnosis and requirement for revascularisation are decided by a vascular surgeon and recorded in the patient’s medical record. This decision is based on clinical symptoms and circulatory assessments, including the ankle brachial index (ABI), Duplex ultrasound, and/or computed tomography angiography. Cessation of smoking for at least 3 months prior to surgery is required. Patients are prescribed statins and antiplatelet agents at this point if not previously prescribed.

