#### Adherence to medication

The primary outcome, adherence to medication, is defined as adherence to prescribed antithrombotic agents and lipid modifying agents 1 year after revascularisation.

The Swedish Prescribed Drug Registry (PDR) will be used for collecting data on medication adherence. The PDR provides data on prescribed drugs containing information on dispensed items, dispensed amount, dosage, and expenditure. Furthermore, this registry has been linked to the civic registry number since 2005 and thus provides information on an individual basis. This registry does not include medications that are prescribed and administered in hospitals [31]. Data from a period of 18 months (6 months before to 12 months after revascularisation) will be retrieved from the PDR for each participant. The WHO Collaborating Centre for Drug Statistics Methodology classification of Anatomical Therapeutic Chemical (ATC) codes will be used to identify antithrombotic agents and lipid-modifying agents (see Table 1 for specific codes). Although antihypertensive medications will not be included in the analysis for primary outcome, they can be considered as BMT for patients with hypertension. Information on antihypertensives will be retrieved from the PDR as medication of interest for the study. We will also collect patient-reported adherence to medication (anticoagulant agents, antiplatelet agents and lipid-lowering agents) at study enrolment and at 1 year after revascularisation.

**Table 1 Tab1:** Medications of interest in the study

Medication group	ATC Code
Antithrombotic agents	
Vitamin K antagonists	B01AA
Heparin group	B01AB
Platelet aggregation inhibitors excluding heparin	B01AC
Direct thrombin inhibitors	B01AE
Direct factor Xa inhibitors	B01AF
Lipid-modifying agents	
HMG CoA reductase inhibitors	C10AA
Fibrates	C10AB
Other lipid-modifying agents	C10AX
Antihypertensives	
Diuretics	C03
Beta-blocking agents	C07
Calcium channel blockers	C08
ACE inhibitors, plain	C09A
ACE inhibitors, combinations	C09B
Angiotensin II antagonists, plain	C09C
Angiotensin II antagonists, combinations	C09D

legend: Medications of interest in the study and their Anatomical Therapeutic Chemical (ATC) codes according to the WHO Collaborating Centre for Drug Statistics Methodology (WHOCC) classification*.*

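### Pre-surgery registry dispensing is collected but has no stated role in the primary analysis, and adjustment is justified by confounding rather than by prognostic covariates fixed in advance

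*Protocol article*

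**What the plan says.** All references are to the protocol article.

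- **Statistical analysis** assigns chi-square or Fisher's exact test to categorical data, and then adds: "Logistic regression analysis will be performed for binary outcomes to adjust for confounding factors". Adherence, as the trial was sized, is both categorical and binary, so both sentences apply to it. Neither is called primary, and the adjustment factors are not named.
- **Sample size** rests on an "increase in adherence to prescribed BMT from 50 to 70% (power, 0.80; significance value, 0.05; two-sided". The section "showed that a required sample size of 186 participants was needed", and continues: "We plan to recruit 210 participants and expect a 10% drop-out".
- **Adherence to medication** defines the outcome on antithrombotic and lipid-modifying agents and states: "Data from a period of 18 months (6 months before to 12 months after revascularisation) will be retrieved from the PDR". Patient-reported adherence is also collected at enrolment. The article assigns no analytic role to the pre-surgery data.
- **Study design and setting** says of the first clinic visit: "Patients are prescribed statins and antiplatelet agents at this point if not previously prescribed". Established users and newly treated patients can therefore both enrol.
- **Randomisation** has patients "randomised to either the intervention group or the control group", without blinding.

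**The concern.** After randomisation, a baseline difference between the arms arises by chance. Calling the adjusters confounding factors suggests choosing them because they turned out unequal, which can only be seen once the data are in. The better reason for adjusting is that a covariate predicts the outcome strongly. It can then be named in advance, and it improves precision whether or not the arms happen to be balanced on it.

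Earlier dispensing of the same drugs is the natural candidate here. It is the same construct from the same source, and it separates established from new users. Two things are at stake:

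- power that data already being collected could supply;
- protection against a choice between an unadjusted and an adjusted p-value, in an open-label trial whose recruitment is already complete.

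**Working it through.** **1. The plan's own figure.** Inputs from the Sample size section are 50% versus 70%, two-sided 0.05 and power 0.80. Equal allocation is an assumption, because the article does not state the ratio. The pooled two-proportion formula per arm is

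n = [z(0.975)·√(2·p̄·(1−p̄)) + z(0.80)·√(p1(1−p1) + p2(1−p2))]² / (p2−p1)²

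with p̄ = 0.60:

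- First term: 1.960 × √0.48 = 1.358
- Second term: 0.842 × √0.46 = 0.571
- n = (1.929)² / 0.04 ≈ 93 per arm, or 186 in total

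This matches the stated figure exactly. Drop-out is also covered: 186/0.9 = 207, and 210 × 0.9 = 189 evaluable, for a power of 0.806. The size is therefore that of an unadjusted comparison, and it is correct.

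**2. Effect of adjusting for baseline adherence.** The article gives neither the share adherent before surgery nor its correlation phi with 1-year adherence. Both are assumptions, shown over a range. The simulations used one binary baseline covariate and overall rates of 50% and 70%, and compared the unadjusted test with logistic regression on arm and baseline.

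| Assumed phi | Power unadjusted | Power adjusted, 93 per arm (50% or 65% adherent at baseline) | Approximate N for 80% power: 186 × (1 − phi²) |
|---|---|---|---|
| 0 | 0.79–0.80 | 0.79–0.80 | 186 |
| 0.2 | 0.81 | 0.82 | 179 |
| 0.3 | 0.80 | 0.84–0.85 | 170 |
| 0.4 | 0.80 | 0.87 | 157 |
| 0.5 | 0.78–0.80 | 0.90–0.91 | 140 |
| 0.6 | 0.79–0.80 | 0.94 | 120 |

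A second set used 94 per arm, half adherent at baseline, and a constant conditional odds ratio. Control adherence at 1 year is split by baseline status (adherent/not adherent):

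| Control split | phi in controls | Power, unadjusted to adjusted | Conditional odds ratio |
|---|---|---|---|
| 60%/40% | 0.2 | about 0.80 to 0.81 | 2.41 |
| 70%/30% | 0.4 | about 0.80 to 0.86–0.87 | 2.70 |
| 80%/20% | 0.6 | about 0.80 to 0.92 | 3.50 |

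The marginal odds ratio is (0.7/0.3)/(0.5/0.5) = 2.33 throughout. The conditional odds ratio thus moves with the covariate while the risk difference stays at 20 points, which is why the risk-difference scale is easier to read against the design.

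**3. A less favourable baseline.** If 80% are adherent before surgery and 50% of controls at 1 year, phi has a ceiling. The largest possible rate among the baseline-adherent is 0.5/0.8 = 0.625, against 0 among the rest, so phi = 0.625 × √(0.8 × 0.2/0.25) = 0.5. A 56%/25% split gives phi of about 0.25, and simulated power rises by only 2 to 3 points (about 0.79–0.81 to 0.82–0.83).

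**4. Type I error.** With the adjusted test fixed in advance, the simulated error was 0.049–0.055 in the first set and about 0.046–0.052 in the second, so adjustment is safe. If the smaller of the unadjusted and adjusted p-values were taken instead, the error was roughly 0.054–0.061, 0.07 and 0.073–0.076 in the three scenarios of the second set. That is the cost of leaving the order open, with a single candidate covariate.

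**The case against.** The strongest reply is that this is a condensed article. Covariate lists, the order of analyses and the effect measure usually sit in an analysis plan, which is not at hand. The article does not exclude pre-surgery dispensing as an adjuster; it is silent. Chi-square is a valid test of two randomised proportions and matches the sizing. The gain rests on an association that nobody has supplied. Patients first prescribed treatment shortly before surgery also have a short look-back, which weakens the covariate.

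Most of this stands. The missing covariate list is not the point by itself. What remains is the wording that is present, which gives confounding as the ground for adjustment, and the availability of a better method that needs no new data.

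A reader might infer more than the text supports:

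- **That an unadjusted chi-square is the designated primary analysis.** The sizing suggests it, but the article never says so, and the logistic sentence also covers a binary primary outcome.
- **That substantial power is free for the taking.** At phi 0 there is no gain, and at phi 0.2 it is 1 or 2 points.
- **That leaving out site or reporting an odds ratio is an error.** The article describes no stratification by site and does not commit to reporting only an odds ratio. Both are matters of preference.

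The simulations also used one binary covariate, not the three-level version proposed below, so they show the likely size of the gain rather than an exact forecast.

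**Conclusion.** The point holds as an improvement in efficiency and pre-specification. The article offers two analyses of the primary outcome without an order, grounds the adjusted one on confounding, and gives no role to a baseline measure of the outcome that it already retrieves. Nothing planned is invalid, and 186 is right.

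The benefit ranges from none to about 14 points of power as the assumed phi runs from 0 to 0.6. It may be smaller if most patients are already dispensed treatment before surgery or have a short look-back. Confidence is good that adjustment fixed in advance does no material harm and closes an open choice. It is only moderate that the power gain will be large.

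**What to change.** Before outcome data are seen, state one primary analysis: logistic regression of 1-year adherence on arm and pre-surgery registry dispensing, coded as both drug classes, one, or neither in the 6 months before revascularisation. Site may be added. Preferably report a standardised (marginal) risk difference with its 95% confidence interval, which is the scale of the 50% versus 70% design. Keep the chi-square test as supportive. Replace the reference to confounding factors with this fixed list of prognostic baseline covariates.

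If an analysis plan already does this, it is enough to confirm it and align the wording. The cost is text only: the registry extract already contains the data, and the sample size does not change.

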### SPIRIT statement

The protocol has been designed according to SPIRIT Recommendations of the Standard Protocol Items: Recommendations for Interventional Trials [47]. A SPIRIT figure is available for this protocol (Fig. 2).

### Trial status

The FASTIC trial is currently ongoing with data collection in both study sites. Recruitment of participants started in June 2016 and was completed in November 2018.

## Discussion

The global aim of our research project is to reduce cardiovascular-related morbidity and mortality, which is currently one of the largest public health problems. In the FASTIC study, we will target patients with IC, which is a cohort with high risk of future cardiovascular and cerebrovascular events. Furthermore, most patients with IC are of older age and a recent review stated that there is a knowledge gap on optimal strategies for primary and secondary prevention of cardiovascular disease among older adults (> 75 years) [48]. The authors also concluded that there is a need for clinical trials using novel study designs with person-centred outcomes.

The concept of person-centred care has been highlighted recent years, and there is an increasing demand from national authorities to improve the quality of care by adapting health care to a more person-centred model. The FASTIC study can contribute to knowledge on how to implement person-centred care in a clinical context. We also believe that the results from our study can provide important information about interventions aimed to improve adherence to medication, which is an unexplored field among patients with IC, and other secondary prevention and risk reduction therapies.

The clinical context of the FASTIC study can be both a strength and a limitation. The methods used and evaluated in this study can be easily implemented in other clinical settings. However, uncontrolled conditions and events that may occur in a clinical context can affect the reliability of the results. The diversity of interventions in the intervention programme may also appear to be a reliability problem, but this is an inevitable consequence of personalised care that is fundamental in person-centred care.

Attrition, loss of participants during the intervention could be a potential threat to the internal and external validity in RCTs. The expected drop-out rate for this RCT is 10% and is taken into account in the sample size calculation. Furthermore, to reduce the risk of response burden we have based decision on use of questionnaire on the content rather than the length per se which is also described as preferable [49]. Process evaluation within studies can be used to assess fidelity and quality of implementation, clarify causal mechanisms and identify contextual factors associated with variation in outcomes [50]. Attendance and notes on reasons for absence at individual visits will be recorded continuously. The intervention is theory driven and the nurses are specially trained in PCC approach and in MI. A qualitative interview study is planned with the aim of exploring the participants‘experiences after attending 1 year of the FASTIC study.

